### Exclusion criteria

3.2

Having any concurrent rheumatic disease, such as systemic lupus erythematosus, Sjogren's syndrome, or severe osteoarthritis.Having tumor and cancer.Having a history of serious allergic reactions.Pregnant or lactating women and women of childbearing age who do not have an effective contraceptive method.Having cardiac, hematologic, respiratory, neurological, endocrine, renal, hepatic, gastrointestinal, or psychotic disease.Having infectious diseases.Showing poor compliance, and unwillingness to be followed-up.Showing alcoholism or drug dependency.

### Interventions

3.3

Experimental group (HGWG group): Patients are given HGWG (orally twice a day for 12 weeks and instructed to dissolve one package (4 g) with hot water (200 mg). Control group: HGWG placebo will be used in the same way.

Supportive therapy of two groups:

1.DMARDs can be used during the observation period, such as MTX and sulfasalazine (the original dose will be maintained);2.According to the patient's pain severity, NSAIDs can be added;3.Patients should provide a detailed list of drugs used during follow-up and observation period. Researchers must record the name of the drugs, dosage, frequency, and duration.

### Randomization and allocation

3.4

Shanghai Medical Clinical Research Center (CRC) will control the randomization develop a random number table by SAS9.1 PROC PLAN. The random number table will be generated in a ratio of 1: 1 using 3 test centers as a stratification factor. This table contains 2 corresponding groups, one is sequence number of inclusion, the other one is the treatment or placebo group.

Pharmaceutical factory will contact the CRC to obtain the random number table, then post the sequence number to boxed of medicine (HGWG or placebo) according to the table.

When a participant is recruited in, the investigator will make a central telephone call and give him/her the medicine (HGWG or the placebo) from the administrator according to the central call.

All the investigators except for the CRC and pharmaceutical factory will not know the corresponding relations between sequence numbers and different groups until the trials completed.

### Blinding

3.5

In this trial, all the researchers will not be in contact with the CRC and the pharmaceutical factory. The CRC will be isolated from all researchers. The stuff in the pharmaceutical factory does not participant in the other parts of this trial. Therefore, the investigator, doctors, nurses, statisticians (analyze outcomes), and other participants have no access to the research information, and will not know the corresponding relations between sequence numbers and different groups until the whole trial completed (including the statistical work).

If an adverse event is claimed, we will record it and provide a proper treatment strategy. Clinicians will provide emergency services in case of serious adverse events, and report them to the Institutional Review Board within 24 hours. Then the leader of Longhua Hospital ethic committee, CRC and the main investigator will make a decision to break the blinding or not, and the participant information of intervention, HGWG or HGWG placebo will be provided by CRC.

## Outcome measures

4

### Primary outcome measure

4.1

ACR50 from baseline to 12 weeks after treatment will be compared. ACR50 is a standard to describe RA symptoms.^[9]^ ACR 50 is met when the number of tender joints reduces by ≥50%, the number of swollen joints by ≥50%, and at least 3 of the following 5 indexes improves by ≥50%:

Patient's assessment on arthritis pain using a Visual Analogue Scale (VAS) of 0 to 100 mmPatient's global assessment of disease activity using VAS scale (0–10)Patient's assessment of physical function and disability HAQ-DIErythrocyte sedimentation rate (ESR)C-reactive Protein (CRP) level

Similarly, ACR20 is met when ≥20% is achieved in the reduction of tender joint number, swollen joint number, and indexes of 3 of the 5 other measurements.^[10]^

ACR scale has been accepted as the efficacy benchmark in RA clinical trials and has greater discriminant capacity to distinguish patients on active treatment from placebo control.^[9,11,12]^ Here we choose ACR50 as the primary index for that ACR50 can provide more useful information than ACR 20/70.^[13,14]^

### Secondary measurements

4.2

The secondary outcomes will be to compare the rates of change in the ACR20/70, DAS28, HAQ-DI, Patient Assessment of Arthritis Pain, Patient Global Assessment of Arthritis, and AIS score from baseline to 2 weeks, 4 weeks, 8 weeks, 12 weeks, 24 weeks’ and 48 weeks’ follow-up. The rate of change in the ACR50 from the baseline to 2 weeks, 2 weeks, 4 weeks, 8 weeks, 12 weeks, 24 weeks’ and 48 weeks’ follow-up are also secondary outcome measures. Additionally, the change in score on the 36-item Short-Form Health Survey Questionnaire (SF-36) from baseline to 4 weeks, 8 weeks, 24 weeks, and 48 weeks is also calculated.

The DAS28 is an index calculating the number of painful and swollen joints (28 joints, i.e. shoulders, elbows, wrists, metacarpophalangeal and proximal interphalangeal joints, and knees), ESR and the score of global assessment.^[15]^ The formula of DAS 28 is 0.56 × √(28 painful joint count) + 0.28 × √(28 swollen joint count) + 0.70 × (ln ESR) + 0.014 × GH. ESR refers to ESR. GH is the patient's general health visual analog scale (0–10 mm).^[16–18]^

HAQ-DI is a subscale of ACR 20/50/70 that reports biochemical and physical conditions. It has been widely used in RA clinical trials to assess disease activity and patient disability.^[19]^ The HAQ-DI measure shave eight dimensions of functional activity: pruning, dressing, rising, eating, walking, personal hygiene, reach, grip, and other routine activities. Each item has 4 degrees ranging from 0 to 3. “0” refers to “no functional difficulty”, “1” to a bit of functional difficulty, “2” to very much functional difficulty, and “3” to no ability to work. HAQ-DI score 0 to 1 means mild to moderate functional difficulty; 1 to 2 means moderate to severe disability; and 2 to 3 means generally severe disability.^[20]^

People with RA often have sleep disorders that worsen as RA deteriorates.^[10,21]^ The Athens Insomnia Scale (AIS) can help patients quantitatively self-evaluate sleep disorders with a psychometric instrument that includes eight indicators for sleep induction, awakenings during the night, final awakening, total sleep duration, sleep quality during the night, wellbeing during the night, functioning capacity during the day time, and sleepiness during the day time. The score for each indicator ranges from 0 to 3, and the total score is 24 points. The higher the score, the worse the sleep quality, and vice versa.^[22]^

The SF-36 measures eight dimensions, including vitality, body function, body aches, general health perceptions, body functions, emotional function, social function, and mental health. SF-36 is widely used in the evaluation of quality of life in patients with RA.^[10,23]^

In addition, concomitant medications are also recorded as secondary outcomes.

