### Inclusion criteria

3.1

Participants meeting the following requirement will be included.

Diagnosed with RA according to the diagnostic criteria developed by the American College of Rheumatology in 1987.DAS28 score of 2.6 to 5.1.Aged 18 to 70.Signing informed consent and ensuring test compliance.Women of childbearing age must undergo testing and have no pregnancy plan throughout the trial.Having no history of combined disease and active tuberculosis.

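### The DAS28 formula pairs the weight 0.014 with a 0–10 general-health scale and states no conversion; scored as printed, the general-health term spans 0.14 units instead of 1.40.

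*Protocol article*

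**What the plan says.** Section 4.2 (Secondary measurements) of the protocol article describes DAS28 as an index built from painful and swollen joint counts, "ESR and the score of global assessment". The formula is "0.56 × √(28 painful joint count) + 0.28 × √(28 swollen joint count"), followed by "0.70 × (ln ESR) + 0.014 × GH". GH is defined directly afterwards as the patient's "general health visual analog scale (0–10 mm").

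Section 4.1 (Primary outcome measure) lists the ACR components. The patient global is given as "global assessment of disease activity using VAS scale (0–10"), without a unit. In the same list the pain scale runs from 0 to 100 mm.

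DAS28 has two uses. Section 3.1 (Inclusion criteria) requires a "DAS28 score of 2.6 to 5.1". Section 4.2 makes it a secondary outcome, where the plan is to "compare the rates of change in the ACR20/70, DAS28, HAQ-DI" and other measures from baseline to 2, 4, 8, 12, 24 and 48 weeks.

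No section gives a conversion from 0–10 to 0–100, or a 0–100 GH scale.

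**The concern.** The weight and the scale do not fit each other. In the standard DAS28-ESR the weight of 0.014 applies to GH in millimetres on a 0–100 mm line. That is general method knowledge, and the article does not state it. The article's own figures point the same way. Global assessment is named as one of four components, yet on a 0–10 scale the worst possible health would add 0.14, a quarter of what one tender joint adds (0.56 × √1 = 0.56).

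Two things are at stake. The first is the entry criterion: a score that is too low, by an amount that grows with patient-reported severity, moves patients across both limits of the window. The second is the DAS28 outcome: nine tenths of any improvement in GH would drop out of the score. A mis-scored outcome can be recalculated later if the components are recorded, but a mistaken enrolment cannot be undone.

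**Working it through.** The article gives no worked DAS28 value to reproduce, so the check applies its formula on both scales.

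**Inputs from the article.** Weights 0.56, 0.28, 0.70 and 0.014, and GH on 0–10 (section 4.2); entry window 2.6 to 5.1, width 5.1 − 2.6 = 2.5 (section 3.1).

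**Inputs that are assumptions.** The 0–100 mm reference scale (standard method knowledge), and every patient value below. The article gives no distribution of GH, joint counts or ESR.

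**1. Range of the GH term**
- As printed: 0.014 × 10 = 0.14
- On 0–100: 0.014 × 100 = 1.40

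**2. Weight within the index** (28 joints, ESR = 100 assumed as an upper value)
- Tender joints: 0.56 × √28 = 2.96
- Swollen joints: 0.28 × √28 = 1.48
- ESR: 0.70 × ln 100 = 3.22
- GH share of the maximum as printed: 0.14 / 7.81 = 1.8%
- GH share on 0–100: 1.40 / 9.07 = 15.4%

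**3. Shortfall per patient**

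For GH in mm, an unconverted 0–10 score equals GH/10. The shortfall is 0.014 × (GH − GH/10) = 0.0126 × GH.

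| GH (mm) | Shortfall | Share of the 2.5-unit window |
|---|---|---|
| 30 | 0.38 | 15% |
| 50 | 0.63 | 25% |
| 70 | 0.88 | 35% |
| 100 | 1.26 | 50% |

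**4. Entry window**

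If GH were 50 mm, a printed score of 5.10 would correspond to 5.10 + 0.63 = 5.73 on 0–100, and a printed score of 2.60 to 2.60 + 0.63 = 3.23. Patients between 5.10 and 5.73 on the 0–100 scoring would be let in, and those between 2.60 and 3.23 kept out.

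Two illustrative patients with assumed values:
- 8 tender joints, 5 swollen, ESR 35, GH 60 mm. The joint and ESR terms sum to 1.58 + 0.63 + 2.49 = 4.70. As printed, adding 0.08 gives 4.78 (inside the window). On 0–100, adding 0.84 gives 5.54 (outside).
- 1 tender joint, 0 swollen, ESR 12, GH 30 mm. The terms sum to 0.56 + 0 + 1.74 = 2.30. As printed, adding 0.04 gives 2.34 (outside). On 0–100, adding 0.42 gives 2.72 (inside).

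**5. Change score**

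A 30 mm improvement in GH contributes 0.014 × 3 = 0.042 as printed and 0.014 × 30 = 0.42 on 0–100, a tenfold cut. The joint and ESR contributions do not change.

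**6. Primary endpoint**

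ACR50 uses percentage improvement in each component. For a patient global falling from a to b, (10a − 10b)/10a = (a − b)/a, so the result is the same on 0–10 and 0–100. DAS28 is not an ACR component, and the sample size rests on ACR50 rates (section 2.5).

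**The case against.** The strongest reply is that this may be a printing slip. A 10 mm line is hardly a usable instrument, so the text could mean 0–100 mm with a zero lost, or 0–10 cm with the wrong unit. The case report form and the scoring instructions are not shown, and nothing proves that an unconverted 0–10 value will be entered. This stands as a condition: the harm arises only if the formula is applied as printed. It does not remove the point. The 0–10 range appears in section 4.1 as well as 4.2, a 10 cm line scored 0–10 gives the same error, and three centres could each resolve the wording differently.

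A second reply is that the article nowhere ties 0.014, or the limits 2.6 and 5.1, to a 0–100 scale. That is true. The premise is standard knowledge of the index, supported inside the article only by the very small GH term and the mixed scale formats.

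A reader might also infer more than the article supports:
- **That the wrong patients will be enrolled.** This depends on how the score is actually computed, and their number depends on GH values that the article does not give.
- **That the DAS28 comparison is biased towards one arm.** Both arms of a randomized, double-blind trial are scored by the same rule. Part of any effect is lost in the same way in each arm.
- **That the primary result or the sample size is wrong.** Neither uses DAS28. A shift at entry happens before randomization, so it could change the case mix in which ACR50 is measured but would not break the comparison.

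**Conclusion.** The scoring rule is wrong as written: a weight of 0.014 is paired with a 0–10 scale and no conversion is stated. Applied literally, it caps the GH term at 0.14 instead of 1.40 and lowers DAS28 by 0.0126 × GH in mm, or 0.38 to 0.88 for GH of 30 to 70 mm.

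It would misclassify some patients near both entry limits and cut the GH contribution to DAS28 change tenfold in both arms. The second effect is attenuation. The ACR50 endpoint and the sample size are unaffected.

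The conclusion rests on two assumptions: that 0.014 is the standard weight for a 0–100 mm scale, and that an unconverted 0–10 score would be entered. The GH values are illustrations. The proportion of patients misclassified cannot be derived from the article.

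**What to change.** In section 4.2, either define GH as a 0–100 mm scale, or state that a 0–10 score is multiplied by 10 before 0.014 is applied. Say there whether GH is the same item as the patient global in section 4.1, so that the two descriptions agree. Make clear that the DAS28 in section 3.1 is calculated by the rule in section 4.2, and use one calculation at screening and at every visit in all three centres.

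The patient global scale in section 4.1 need not change for ACR scoring, because percentage improvement does not depend on the scale.

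The cost is a one-line correction to the protocol, plus a matching note on the case report form. It is best made before the first patient is screened. After that, DAS28 outcomes can still be rescored from the recorded components, but entry decisions already taken cannot be reversed.

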### Safety assessments

4.3

The HGWG has been used for hundreds of years in China, and the quantity of herbs in the HGWG are safe according to the recommended amount in Pharmacopoeia of the People's Republic of China (2015 version). The incidence and severity of adverse reactions are observed in each test. Clinical tests on joint swelling, tenderness, morning stiffness, and average grip strength will be observed closely along the whole trial. Also, the laboratory tests, blood routine, urine routine, feces routine, kidney, and liver function will be performed at the beginning and end of this trial.

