**Table 1 T1:**
[figure not shown]
Components of HGWG.

Anti-rheumatic drugs (DMARDs), such as methotrexate (MTX) and sulfasalazine, may be used during the observation period. Patients’ original records are recorded. Non-steroidal anti-inflammatory drugs (NSAIDs) may be used to control patient's pain. The doctor responsible for the project will keep all medication records during the patients’ treatment. In addition, other conditions and treatments should be documented in the management manual. Both groups will have a 3-month treatment and a 9-month follow-up. At 7 time points (baseline, 2 weeks, 4 weeks, 8 weeks, 12 weeks, 24 weeks, and 48 weeks), visits will be scheduled for each patient. The plan is shown in Table 2.

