### Data collection and monitoring

4.5

This is a 48 weeks’ clinical trial in which participants will receive 12 weeks of medication and 36 weeks of follow-up. Disease activity will be assessed at 7 time points (baseline, 2 weeks, 4 weeks, 8 weeks, 12 weeks, 24 weeks and 48 weeks). Longhua Hospital affiliated with Shanghai University of Traditional Chinese Medicine (http://www.longhua.net/ywsy/gzlc/287.jhtml) is responsible for quality control and training for investigators.

Epidata (version 3.0) procedure will be used to restrict data values. Two trained investigators will enter and compare the data independently to rule out the difference.

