### Statistical analysis

4.6

Trained statisticians will adopt intention-to-treat approach for effectiveness and safety analysis. In addition, the last-observation-carried-forward method will be applied in handling missing values. All statistical analysis will be conducted by Statistical Packages of Social Sciences (SPSS) software (version 22.0). Statistical test is two-sided and *P* < .05 is statistically significant. The mean ± standard deviation will be used for the description of continuous variables. The percentage is used to categorize the variable's description. Continuous variables following the normal distribution will be analyzed by Student *t* test; otherwise, non-parametric tests will be used to compare group differences.

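### Read literally, the only post-baseline safety laboratory panel comes 36 weeks after the last dose, and carrying the last observation forward would record a missing one as no change

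*Protocol article*

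**What the plan says.** Section 4.3 (Safety assessments) names blood, urine and feces routine tests and kidney and liver function. It gives them two time points: "kidney, and liver function will be performed at the beginning and end of this trial". The same paragraph says of clinical events: "The incidence and severity of adverse reactions are observed in each test".

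Section 4.5 (Data collection and monitoring) describes a 48-week trial in which "participants will receive 12 weeks of medication and 36 weeks of follow-up". Section 2.2 (Medication and administration) agrees, counting four weeks to the month: "Both groups will have a 3-month treatment and a 9-month follow-up". Visits are at baseline and weeks 2, 4, 8, 12, 24 and 48.

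Section 4.6 (Statistical analysis) covers safety by name: "Trained statisticians will adopt intention-to-treat approach for effectiveness and safety analysis". Its next sentence adds that "the last-observation-carried-forward method will be applied in handling missing values". No data type is exempted.

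**The concern.** Evaluating safety is a stated purpose of the trial (section 2.1). Scheduled laboratory tests exist mainly to find changes that cause no symptoms and so would not be reported as adverse events. If the one post-baseline panel is drawn long after exposure ends, it shows only what has lasted until then. It also follows 36 weeks in which patients may take background anti-rheumatic drugs and added pain relief but no study product, so an abnormality found then is hard to attribute.

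The missing-data rule adds a second problem. With one value before and one after, carrying the last observation forward means carrying the baseline forward. Patients without a final panel enter the comparison as unchanged although nothing was measured. Both features pull the laboratory comparison towards no difference between arms.

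**Working it through.** **Inputs from the Protocol article.** Trial length is 48 weeks, with 12 on medication and 36 of follow-up (4.5). There are two laboratory time points (4.3). Each arm has 60 patients and the loss allowance is 20% (2.5). LOCF applies to missing values (4.6).

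**Plan's own figure.** 12 + 36 = 48 weeks, which reproduces the stated length.

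**Gap from last dose to final panel.** 48 − 12 = 36 weeks, or 36 × 7 = 252 days. Four visits (weeks 2, 4, 8 and 12) fall within the treatment period, and the text of section 4.3 assigns the panel to none of them.

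**Effect of LOCF with two draws.** The carried value equals baseline, so change = baseline − baseline = 0. At 20% loss this affects 0.20 × 60 = 12 patients per arm, 24 of 120 in all. This is the most that a 20% loss can produce, because a sample taken at withdrawal would reduce it.

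**Illustration of the loss of information.** Let q be the true on-treatment abnormality rate, s the share of abnormalities still present at week 48, and d the loss. The documents give neither q nor s, so both are assumptions. If loss is unrelated to toxicity:

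- rate recorded as written = q × s × (1 − d)
- expected cases per arm = 60 × that rate
- chance of seeing at least one = 1 − (1 − rate)^60

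| Panel | q = 10%: cases, P(≥1) | q = 5%: cases, P(≥1) |
|---|---|---|
| Abnormality present when sampled, no loss | 6.0, 0.998 | 3.0, 0.954 |
| Week 48, d = 20%, s = 1 | 4.8, 0.993 | 2.4, 0.914 |
| Week 48, d = 20%, s = 0.5 | 2.4, 0.914 | 1.2, 0.702 |
| Week 48, d = 20%, s = 0.25 | 1.2, 0.702 | 0.6, 0.453 |
| Week 48, s = 0 | 0, 0 | 0, 0 |

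The two causes can be separated at q = 10%:

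- **Timing alone (d = 0):** expected cases are 6.0, 3.0, 1.5 and 0 as s falls from 1 to 0.5, 0.25 and 0.
- **LOCF alone (s = 1):** the 4.8 cases are divided by 60 instead of by the 48 patients measured. That gives 4.8/60 = 8% where observed values give 4.8/48 = 10%, a relative dilution of 20%. Dropping LOCF does not recover unmeasured cases, but it stops counting those patients as normal.

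If patients leave because of toxicity, the dilution is larger than 20%.

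**The case against.** The strongest reply is that Table 2, the schedule of assessments, is not shown. It is where a week-12 panel would be listed, and the end of the trial might loosely mean the end of treatment. This stands as far as it goes: the absence of an on-treatment panel cannot be proved. The definition of the trial as 48 weeks still favours the literal reading. If Table 2 does list week 12, the text of section 4.3 needs correcting to match.

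A reader might infer that toxicity during treatment is hidden altogether. The documents do not support that. Section 4.3 provides for recording the incidence and severity of adverse reactions and for observing clinical signs throughout, and section 3.5 (Blinding) has serious events reported within 24 hours. Nor is the laboratory comparison blind to everything that starts on drug, since persistent abnormalities would still appear at week 48 (4.8 of 6.0 in the illustration).

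A reader might also take the use of intention-to-treat for safety as a further source of concealment. It matters only if patients go undosed or receive the wrong product. Nothing suggests many of either, and section 3.4 describes numbered boxes and central telephone allocation.

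Finally, LOCF is stated in general terms in a condensed article, and an analysis plan may narrow it. That is fair, but section 4.6 names safety in the sentence just before and makes no exception.

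**Conclusion.** The point holds in a limited form. On the plain text of sections 4.3 and 4.5, the only post-baseline laboratory panel is 36 weeks after the last dose, so abnormalities that arise on treatment and resolve by week 48 would go unseen. How many is unknown, because persistence is not given: the loss from timing runs from none, if all persist, to all of them, if none do. Under section 4.6 as written, up to 12 of 60 patients per arm would have their laboratory change set to zero at the assumed 20% loss, a 20% relative dilution if loss is unrelated to toxicity.

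This rests on the literal meaning of the trial's end, on Table 2 not saying otherwise, on LOCF reaching safety data, and on there being no withdrawal sample. It concerns the laboratory safety conclusion only. It does not affect the primary efficacy result or show that clinical adverse events would be missed. It should be corrected because the remedy is cheap.

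**What to change.** 1. **Sections 4.3 and 4.5, and Table 2:** reconcile them so that the end panel is defined relative to the 12-week treatment period and placed at the existing week-12 visit, with week 48 optional. Blood is already needed at week 12 for ESR and CRP in the primary outcome. If the end panel moves to week 12, the number of panels does not change. If week 48 is kept as well, the cost is one added panel per patient, including urine and feces samples that the existing blood draw does not supply.
2. **Section 4.6:** state that safety laboratory and adverse-event data are analysed on observed values, without LOCF, and that the number of patients with a post-baseline panel is reported by arm. This is wording only.
3. **Section 4.6, minor:** base the safety analysis on patients who took at least one dose. This is also wording only.
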